### Random allocation of groups

A consecutive inclusion will be done until the desired sample size is reached. The generation of the random sequence will be carried out by the principal investigator using the statistical software Epidat. The randomization list will be delivered to the clinics reception desk and patients will be allocated by telephone at a 1:1 ratio (assignment by third parties).

Each participant will be assigned an identification number created for the study and linked to his treatment group. This number will allow the patient for beginning the treatment sessions. Two physiotherapists previously trained for the application of the study protocol will be in charge of the sessions.

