## Methods

### Study design

This manuscript describes a research protocol for a single blind, equivalence randomized controlled clinical trial. Equivalence trials aim to determine whether one intervention is therapeutically similar to another; equivalence is defined as the treatment effect being between − Δ and + Δ, Δ meaning the margin of equivalence. If the confidence interval of the outcomes difference between the two studied groups falls within the predetermined margin of equivalence (− Δ to + Δ), the two types of techniques can be considered equivalent. Participants will be randomly allocated into surface electrodes group (intervention group, IG) and intra-anal probe group (control group, CG). The investigator performing the statistical analyses will be blinded.

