### Selection of the sample

The selection of the sample will be done by sampling of consecutive cases, from RAPbarcelona clinic and Institut Médic Tecnológic in Barcelona. In urologists or physiotherapists appointments, patients who underwent radical prostatectomy and presented with UI will be referred to the principal investigator. The protocol will be clearly explained to each of the interested patients who meet all the selection criteria and he will be asked to sign the informed consent if accept participation. After the signature the patient will be allocated to one of the two study groups.

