### Collection, management and data analysis

Data will be collected in a specific database for this study by the physiotherapists in charge of the application of the technique and sent to a data analyst unfamiliar with the techniques and study groups. The SPSS 24.0 software will be used.

First, a descriptive analysis of the characteristics of the patients included in both study groups, as well as the outcome variables will be carried out. To do this, absolute and relative frequencies (percentages) will be estimated for qualitative variables, and mean or median and standard deviation or range, respectively, depending on the normality of the distribution, for quantitative variables.

In addition, different associations between diverse variables will be analysed.

To check for the equivalence of the study treatments efficacy, intention to treat (ITT) and by protocol (PP) analysis will be performed.

The comparison of results will be done by estimating the differences in a timely manner and with their corresponding 90% confidence intervals (90% CI). Additionally, the adjusted differences will be calculated, following the indications of the CONSORT document [23].

In all cases, the level of statistical significance established will be the usual (5%); Therefore, statistically significant differences will be considered when p values are less than 0.05.

If adverse effects would occur, the physiotherapist together with the principal investigator will decide the continuity of the participant in the study, having his safety and health as a priority.

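### The principal investigator generates the random sequence and also receives the referred candidates, with nothing stated to keep that role from the list, so allocation may be foreseeable to someone involved in enrolment

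*Protocol article*

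**What the plan says.** Four sections of the protocol article bear on this.

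- **Random allocation of groups**, on who makes the sequence: "The generation of the random sequence will be carried out by the principal investigator using the statistical software Epidat". On what happens next: "The randomization list will be delivered to the clinics reception desk and patients will be allocated by telephone at a 1:1 ratio". The article describes this step as assignment by third parties. Inclusion is consecutive.
- **Selection of the sample**, on the route into the trial: "patients who underwent radical prostatectomy and presented with UI will be referred to the principal investigator". The study is then explained to interested patients who meet the criteria, and they are asked for consent. On timing: "After the signature the patient will be allocated to one of the two study groups".
- **Study design**, on blinding: "The investigator performing the statistical analyses will be blinded". No other role is said there to be blinded.
- **Collection, management and data analysis**, on adverse effects: "the physiotherapist together with the principal investigator will decide the continuity of the participant in the study". The same section has the treating physiotherapists collect the data.

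**The concern.** Allocation concealment requires that nobody who can influence whether, or when, a patient enters the trial can foresee the next assignment. Here one role produces the assignments and also receives the candidates. Anyone who can see both the next line of the list and the next patient could, without any ill intent, encourage, defer or discourage that patient according to the arm that is due.

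Three features of this trial make that worth preventing.

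- The arms differ in acceptability. The Background says that the intra-cavitary route may be unpleasant for the patient, and the Discussion expects the surface route to be more comfortable. There is thus a conceivable reason to match patients to arms.
- Eligibility covers incontinence grades I to III, and the primary outcome is grams of urine lost. Selection by severity would act on a variable closely tied to that outcome.
- Blinding is limited to the analyst. Concealment before assignment is therefore one of the few protections against bias that the design has.

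In an equivalence trial, selection can work in either direction: it can produce an apparent difference between equal treatments or mask a real one.

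**Working it through.** No arithmetic applies. The point depends on who does what and when, and no stated figure changes if it is accepted. The check is to follow the sequence of steps and ask at each one who could know the next arm.

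1. **Generation.** The principal investigator creates the sequence in Epidat (Random allocation of groups). At this moment that role necessarily has access to the whole list.
2. **Transfer.** The list goes to reception (same section). The text does not say that it is sealed or encrypted, or that the investigator keeps no copy. It also does not say that a copy is kept or consulted.
3. **Referral.** Urologists and physiotherapists send candidates to the principal investigator (Selection of the sample). This places that role in the enrolment pathway before allocation.
4. **Explanation, eligibility and consent.** These follow referral, but the sentences are in the passive and name no one. Study population adds that patients are invited at their first physiotherapy visit. That the investigator carries out these steps personally is a fair inference from the referral route, but it is not stated.
5. **Assignment.** After signature, a third party gives the group by telephone. The referring clinicians and physiotherapists do not hold the list, so the next arm is hidden from them at this point. It is not hidden by this step from whoever performed step 1.
6. **After assignment.** The principal investigator shares decisions on whether a participant continues after adverse effects (Collection, management and data analysis). Those decisions come after the arm is known, so they are not a concealment issue. They do show that this role is active in the conduct of the trial.

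Steps 1 and 3 belong to the same role. Step 5 protects against everyone except that role, and no section supplies the missing separation. Because inclusion is consecutive, a position on the list corresponds to the next patient enrolled, so knowledge of the list would be usable.

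**The case against.** The strongest reply is that the plan already has real safeguards. Assignment is by a third party, by telephone and after signed consent, and cases are to be taken consecutively, which limits discretion to defer or skip a patient. All of this stands. It removes the concern for the referring urologists and the treating physiotherapists and narrows it to one role. It does not close the gap for that role, because telephone release conceals a list only from people who have not seen it.

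A second reply is that an article condenses a fuller protocol. That would answer a complaint about missing detail. This is different: the article positively assigns both tasks to the same role.

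A reader might go further than the text allows in four ways.

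- **That the investigator knows the next arm, so allocation is not concealed.** The documents show opportunity. They do not say that the list is kept, remembered or consulted after delivery.
- **That the investigator personally screens and takes consent.** Only the referral is stated.
- **That any resulting bias is beyond repair in the analysis.** An imbalance in baseline pad weight could be partly handled, since it is measured at session 1, the Abstract speaks of changes in the pad test, and adjusted differences are planned, although the covariates are not named. Selection on unmeasured features, such as dislike of the probe, would remain.
- **That one list serves two clinics.** The phrase about the reception desk can equally mean a desk at each clinic. How lists are arranged by site is a separate matter that an article may leave out.

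**Conclusion.** The concern holds in a limited form. The principal investigator generates the sequence and receives the candidates, and nothing stated keeps that role from the list while recruitment is open. Allocation may therefore be foreseeable to someone involved in enrolment, despite third-party assignment after consent.

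This rests on two stated facts, the generation and the referral, and on the absence of any stated barrier between them. It does not assume misuse.

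No numerical size is attached. A reader might be tempted to express the possible bias as a share of the 22 g used in Sample size. That would need an invented number of steered patients and, for any effect on power, a standard deviation that the article does not give. It would also need the assumption that a baseline shift passes gram for gram into the outcome difference. The documents support none of these. The case for change rests on a clear structural weakness and a remedy that costs almost nothing.

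**What to change.** Amend Random allocation of groups in three respects.

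1. An existing member of the institution with no part in referral, eligibility, consent, treatment or analysis generates the sequence and holds it.
2. The principal investigator and the physiotherapists have no access to the sequence until recruitment closes.
3. Reception releases each assignment, one at a time, only after the patient's consent and enrolment have been logged.

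The telephone procedure, the 1:1 ratio and the order of consent before allocation stay as they are. The cost is handing over one short task and adding a few sentences, with no extra patients. If recruitment has already begun, the change should apply to all remaining allocations from a newly generated sequence, and the report should disclose the earlier arrangement.

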### Collection, management and data analysis

Data will be collected in a specific database for this study by the physiotherapists in charge of the application of the technique and sent to a data analyst unfamiliar with the techniques and study groups. The SPSS 24.0 software will be used.

First, a descriptive analysis of the characteristics of the patients included in both study groups, as well as the outcome variables will be carried out. To do this, absolute and relative frequencies (percentages) will be estimated for qualitative variables, and mean or median and standard deviation or range, respectively, depending on the normality of the distribution, for quantitative variables.

In addition, different associations between diverse variables will be analysed.

To check for the equivalence of the study treatments efficacy, intention to treat (ITT) and by protocol (PP) analysis will be performed.

The comparison of results will be done by estimating the differences in a timely manner and with their corresponding 90% confidence intervals (90% CI). Additionally, the adjusted differences will be calculated, following the indications of the CONSORT document [23].

In all cases, the level of statistical significance established will be the usual (5%); Therefore, statistically significant differences will be considered when p values are less than 0.05.

If adverse effects would occur, the physiotherapist together with the principal investigator will decide the continuity of the participant in the study, having his safety and health as a priority.

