**Methods:**

This single-blind equivalence randomized controlled trial will include 70 man who suffer urinary incontinence post radical prostatectomy. Participants will be randomized into surface electrodes group and intra-anal probe group. The groups will receive treatment for 10 consecutive weeks. Outcomes include changes in the 24-h Pad Test, and ICIQ-SF, SF-12 and I-QoL questionnaires. Clinical data will be collected at baseline, 6 and 10 weeks after the first session, and 6 months after the end of treatment.

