#### Primary outcome

##### Magnitude of urinary incontinence

According to the grams of urine collected in a pad with the 24-h Pad Test. This is a quantitative variable (expressed in grams) evaluated in the first, sixth, tenth and eleventh sessions of the study. The Pad test consists of weighing a clean pad in grams (by the same patient), then placing it and weighing it again after an established time (24 h). In case of needing an extra pad before the 24 h are completed, the procedure would be repeated until 24 h were reached. The increase in weight tells us about the severity of incontinence. The values for mild UI are from 1.3 to 20 g, moderate from 21 to 74 g and severe 75 g or more [13, 14].

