### Sample size

To estimate the sample size, we use the randomisation and online databases for clinical trials program of the online computer software Sealed Envelope Ltd. 2001–2015 (https://www.sealedenvelope.com/power/continuous-equivalence/).

For this estimate, alpha values of 5% and beta of 20% (power of 80%) were taken into account. Based on data published in the literature [10, 12], and considering an expected difference in the 24-h Pad Test between the two studied groups of 22 g, 32 patients are needed in each arm of the study. The interpretation is as follows: “if there is truly no difference between the control (ES by intra-anal probe) and intervention (ES by surface electrodes) treatment, then 64 patients are required to be 80% sure that the limits of a two-sided 90% confidence interval will exclude a difference in means of more than 22 g".

Assuming that there could be losses to follow-up, the number of individuals to be recruited will be increased by 10% until reaching 70 patients (35 patients per group).

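### The plan does not say whether the crude or the adjusted pad-weight difference decides equivalence; naming a baseline-adjusted one would gain precision from data already collected

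*Protocol article*

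**What the plan says.** All places are in the protocol article.

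- **Collection, management and data analysis.** Equivalence is to be checked in intention-to-treat and per-protocol sets. The comparison is described as "The comparison of results will be done by estimating the differences in a timely manner and with their corresponding 90% confidence intervals (90% CI". The next sentence is "Additionally, the adjusted differences will be calculated, following the indications of the CONSORT document [23". No covariates are listed, and neither estimate is called primary.
- **Study design.** Equivalence is concluded if the confidence interval for the difference lies between −Δ and +Δ.
- **Sample size.** The margin in use is 22 g. The target is to be "80% sure that the limits of a two-sided 90% confidence interval will exclude a difference in means of more than 22 g", with 32 per arm before losses.
- **Primary outcome.** The variable is defined as "According to the grams of urine collected in a pad with the 24-h Pad Test", measured at sessions 1, 6, 10 and 11. A baseline value is therefore planned for every participant, and the Investigations section confirms this.
- **Abstract, Methods.** The wording is "Outcomes include changes in the 24-h Pad Test", which suggests change from baseline rather than grams at follow-up.

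**The concern.** One confidence interval decides an equivalence trial, so both its width and its source matter. The word order puts the plain difference first and adjustment second, but the text does not settle which is compared with ±22 g. With crude and adjusted estimates in two analysis sets, four intervals could be read against the margin, and they need not agree.

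The form of the outcome is also loose. Follow-up grams, change from baseline and a baseline-adjusted difference estimate the same arm effect under randomisation, but with different precision. Participants range from mild to severe leakage and may be up to a year after surgery, so session 1 pad weight plausibly predicts later pad weight. If it does, a deciding analysis that leaves it out gives a wider interval than necessary.

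**Working it through.** **Inputs.** From Sample size: margin 22 g; 5% for each one-sided test (equivalent to a two-sided 90% interval); power 80%; true difference 0; 32 per arm. Not stated: the SD and the correlation r between baseline and follow-up pad weight. The SD is back-solved below, and r is shown over a range.

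**1. Reproduce the plan's figure.** For equivalence of two means with true difference 0:

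n per arm = 2 × [SD × (z₀.₉₅ + z₀.₉₀) / 22]², with z₀.₉₅ + z₀.₉₀ = 1.645 + 1.282 ≈ 2.926.

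SD = 30 g gives 2 × (30 × 2.926 / 22)² = 31.85, rounded up to 32. Any SD from 29.6 to 30.07 g gives 32. Other formulas reach about 32 with other SDs: 35.4 g with z₀.₉₅ + z₀.₈₀, or 31.4 g with z₀.₉₇₅ + z₀.₈₀. The formula used here matches the interpretation printed in the article, so 30 g is taken as a working assumption.

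**2. Crude follow-up comparison, 32 per arm.**

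SE = 30 × √(2/32) = 7.5 g.

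Power = 2Φ(22/7.5 − 1.645) − 1 = 2Φ(1.288) − 1 ≈ 80.2% (79.1% using the t distribution).

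90% CI half-width = 1.645 × 7.5 = 12.34 g.

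**3. Alternatives at the same n.**

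ANCOVA residual SD = 30 × √(1 − r²). Change-score SD = 30 × √(2(1 − r)), taking 30 g as the SD of a single measurement and equal variances at both times.

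Example at r = 0.5: residual SD 25.98 g, SE 25.98 × 0.25 = 6.495 g, power = 2Φ(22/6.495 − 1.645) − 1 ≈ 92%.

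| r | ANCOVA SD (g) | ANCOVA n per arm for 80% | ANCOVA power at 32 | ANCOVA 90% CI half-width (g) | Change SD (g) | Change n per arm for 80% | Change power at 32 |
|---|---|---|---|---|---|---|---|
| 0 | 30.00 | 32 | 80% | 12.34 | 42.43 | 64 | 33% |
| 0.2 | 29.39 | 31 | 82% | 12.09 | 37.95 | 51 | 50% |
| 0.3 | 28.62 | 29 | 85% | 11.77 | 35.50 | 45 | 60% |
| 0.5 | 25.98 | 24 | 92% | 10.68 | 30.00 | 32 | 80% |
| 0.6 | 24.00 | 21 | 96% | 9.87 | 26.83 | 26 | 90% |
| 0.7 | 21.42 | 17 | 99% | 8.81 | 23.24 | 20 | 97% |
| 0.8 | 18.00 | 12 | >99% | 7.40 | 18.97 | 13 | >99% |

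Powers are normal approximations. With the t distribution and one degree of freedom spent on the covariate, ANCOVA power is 81% at r = 0.2, 84% at 0.3, 91% at 0.5 and 98% at 0.7.

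**4. Why the ordering does not depend on r.** 1 − r² = (1 − r)(1 + r), and 1 + r never exceeds 2, so the ANCOVA variance never exceeds the change-score variance 2(1 − r). It also never exceeds the crude variance, because 1 − r² ≤ 1. A change score is less precise than plain follow-up grams when r is below 0.5 and more precise above it.

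**The case against.** Three stronger readings are tempting, and the documents support none of them.

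- **A reader might infer that baseline leakage goes unused.** That is not established. The adjusted differences may include baseline pad weight, since no covariates are named, and the changes mentioned in the Abstract would use it by subtraction.
- **A reader might infer that the crude difference is the declared primary analysis.** The article ranks neither estimate. That reading rests on the order of two sentences and the word that opens the second.
- **A reader might infer that the trial loses power against its own target.** It does not. At the back-solved SD, the crude comparison of follow-up grams gives 79–80%, as planned. What is given up is precision relative to a better option.

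It is also fair to say that a crude comparison in a randomised trial is valid, that listing covariates is commonly left to a fuller protocol or analysis plan, and that the Abstract's phrase may only be shorthand covering the pad test and three questionnaires. The missing covariate list is therefore not an error in itself, and the mismatch between the Abstract and the outcome section is minor.

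The size of the benefit is uncertain too. At r = 0.2 the gain is about 2 percentage points, and nothing in the documents shows that r is larger.

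What remains is that the article itself sets out two kinds of estimate without saying which decides, when a choice that is never less precise, apart from one degree of freedom, is available from data it already plans to collect.

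**Conclusion.** The point holds as a free improvement, not as an error that undermines the design. The text leaves open which estimate is compared with ±22 g, and its word order favours the less precise one.

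With 32 per arm, a 22 g margin and an assumed SD of 30 g, naming a baseline-adjusted estimate would raise power from about 80% to 82% at r = 0.2, 85% at r = 0.3, 92% at r = 0.5 and 99% at r = 0.7. The 90% CI half-width would fall from 12.3 g to 10.7 g at r = 0.5 and to 8.8 g at r = 0.7. If the Abstract's wording were taken literally and a change score decided, power would be about 60% at r = 0.3.

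These figures rest on an unstated SD, an unstated r and, for the change score, 30 g being the SD of a single measurement. The direction of the comparison does not depend on those values, but the size of the gain does and cannot be known from the documents.

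**What to change.** In Collection, management and data analysis, name one deciding estimate: the arm difference in follow-up 24-h pad weight from ANCOVA adjusted for baseline 24-h pad weight, with its 90% confidence interval compared with ±22 g. Keep the crude difference with its 90% interval as a sensitivity analysis.

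Align the Abstract with the primary outcome section by referring to pad weight at follow-up adjusted for baseline. With baseline as a covariate, the arm difference is the same whether the response is follow-up grams or change, so this settles the wording without altering what is estimated.

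Time since surgery and centre are optional further covariates, since the documents show no gain from either. Which follow-up visit decides is a separate question that this change does not answer.

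The cost is a sentence or two in the analysis section and a few words in the Abstract. No extra patients, visits or measurements are needed, and the sample size can stay as it is.
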